#### **8.2 Cerebral NIRS monitoring device**

A summary of the risk analysis for each investigational NIRS device is provided in the relevant IB. To ensure safe application of the device investigators and the involved staff will be trained on how to place the device (see section 9.2). For extended monitoring the sensor should be repositioned at a different location, as often as judged necessary. For infants with scalp oedema, or poor perfusion this may be as often as every 4 hours in order to avoid damage from heat and/or pressure. Optimally, replacement should be done as part of the routine handling of the infant to disturb the infant as little as possible.

Further, if skin irritation does occur, it will be treated according to local clinical practice. Interaction with the drugs applied in this population is not possible.

The requirements specified in ISO14155:2011 "6.9 Investigational device accountability" does not apply to this clinical investigation. All devices are owned by the local institution and not provided by the sponsor.

### **8.3 Data Monitoring and Safety Committee**

An independent Data Monitoring and Safety Committee (DMSC) is established to, during the trial, monitor SUSARs with 'certain' or 'probably/likely' relationship with the cerebral NIRS oximeter or the application of the treatment guideline. The charter for the DMSC will be written prior to inclusion of participants and prior to any analysis. The members of the DSMC are listed under "Data Monitoring and Safety Committee" on p. 9.

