## 8. Assessment of safety

### 8.1 Adverse events and reactions

#### 8.1.1 Definitions

**Adverse events (AE):** any undesirable event occurring to a participant during a clinical trial, whether or not considered related to the trial intervention.

**Serious adverse event (SAE):** any adverse event that results in death, is life-threatening, requires prolongation of existing hospitalisation, result in persistent or significant disability or incapacity, or requires intervention to prevent permanent impairment or damage.

**Adverse reactions (AR) / Adverse device effects (ADE):** all untoward and unintended responses related to the interventions of application of the treatment guideline and/or cerebral oximeter.

**Expected adverse reactions (EAR) / Expected adverse device effect (EADE):** adverse reactions, we expect to be related to the interventions cerebral NIRS oximeter and/or the application of the treatment guideline are:

- Local skin reactions (rashes, burns, etc.).
- Reactions related to the manipulation of the patient during positing and re-positing of the cerebral NIRS oximeter sensors.
  - Accidental displacements of the endotracheal tube or extubation.
  - Accidental displacement of venous or arterial catheters,
  - Severe hypoxia or bradycardia otherwise unexplained.
- Other expected adverse reactions encompass reactions to any interventions directed at correcting an out-of-range oximeter reading by improving respiratory status, cardiovascular status, oxygen transport, and blood glucose level (see appendix A).

**Unexpected adverse reactions (UAR):** all untoward and unintended responses, that not is an expected reaction, related to the interventions cerebral oximeter and/or application of the treatment guideline.

**Serious adverse reactions (SAR):** any adverse reaction that results in death, is life-threatening, requires prolongation of existing hospitalisation, results in persistent or significant disability or incapacity, or requires intervention to prevent permanent impairment or damage. This definition includes

**Serious adverse device effect (SADE):** adverse device effect that has resulted in any of the consequences characteristic of a SAE, or are due to

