imprecise or incomplete results from diagnostic equipment e.g. incorrect or delayed diagnosis or incorrect or delayed treatment and **Serious adverse effect-near-incidents (SAE-NI)**: device deficiencies that might have led to a SAE if a suitable action had not been taken, or intervention had not been made, or if circumstances had been less fortunate.

**Expected serious adverse reactions (ESAR)**: any of the expected adverse reactions (listed above) that results in death, is life-threatening, requires prolongation of existing hospitalisation, results in persistent or significant disability or incapacity, or requires intervention to prevent permanent impairment or damage.

**Suspected unexpected serious adverse reaction (SUSAR) / Unanticipated serious adverse device effect (USADE)**: an adverse reaction which is both serious and unexpected, i.e., not identified in the current risk analysis listed above (in expected adverse reactions). Included in this definition are the events with imminent risk of death, serious injury, or serious illness that requires prompt remedial action for other participants, users, or persons (including events that are of significant and unexpected nature such that they become alarming as a potential public health hazard or the possibility of multiple deaths occurring at short intervals) or a new finding to the event.

**Device deficiencies**: malfunction, misuse, or use error, e.g. rStO2 values displayed despite displaced sensor, sensor positioned with light source facing away from skin surface, sudden malfunction of device that result in no or false rStO2-values.

[figure not shown]

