#### 8.1.4 Justification for recording and reporting periodicity and modality

The preterm patient population is a very seriously ill group. Most adverse events may be of a serious nature with or without the SafeBoosC trial intervention, and both intervention groups are expected to have a very high proportion of serious adverse events. It is therefore not possible, nor meaningful to record and report all adverse events. The following will be recorded and reported (for overview refer to table 4):

Adverse reactions (i.e. both expected (EAR) and unexpected (UAR) with a 'certain' or 'probable/likely' relation (see table 3) to the interventions will be recorded together with an assessment and reported with the trial results, The final report clinical investigation report to the competent authorities will summarize the ARs, including a discussion of causal relationship with investigational device, severity, and treatment needed.

Serious adverse events (SAE) to be recorded are: mortality; the mortality is high and will thus be analysed and reported as a secondary outcome measure and thus will not be reported to the authorities, and neonatal morbidities; these are believed to be the most important predictors for later development and health, and are recorded and reported as an outcome measure (necrotising enterocolitis stage 2-3, oxygen requirement, and

retinopathy of prematurity stage 3+ and above, as well as severe intraventricular haemorrhage and periventricular leucomalacia) thus not reported to the competent authorities.

Serious adverse reactions (i.e., both expected (ESAR) and unexpected (SUSAR) related to the cerebral oximeter and/or the treatment guideline will be recorded and analysed as a secondary outcome measure, but only SUSARs will subject to expedited reporting. Due to the nature of the population and the intervention, the near-incidents (**SAE-NI**) will be recorded, but not reported to the authorities.

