### **8.4 Suspension or premature termination of the clinical investigation**

The sponsor/principal investigator, the ECs, and the regulatory authorities can decide about trial continuation. The clinical investigation can be suspended or prematurely terminated if the serious adverse device effects are considered disproportionately large compared to the possible benefits of the intervention. If the trial is terminated or suspended the parents of all trial participants will be informed and appropriate follow-up will be assured. If sponsor/principal investigator terminates or suspends the trial the relevant ECs and regulatory authorities will be provided with a detailed written explanation of the termination or suspension.

The sponsor/principal investigator can upon completion of the analysis of the reason(s) for a suspension decide to lift the suspension, when the necessary corrective actions have been implemented. The investigators, ECs, and relevant regulatory authorities will be notified and provided with the relevant data supporting the decision.

Breaking of blinding will not be relevant in this trial, since group allocation is visible and the assessment of the adverse device effects in the control group are independent of rStO2 readings of the device.

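### Section 8.3 limits the DMSC to SUSARs while section 8.1.1 classes guideline reactions as expected, so most guideline-caused deaths and by-arm mortality have no stated route to the committee

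*Protocol*

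**What the plan says.** Protocol section 8.3 sets up an independent DMSC whose stated task during the trial is to "monitor SUSARs with 'certain' or 'probably/likely' relationship with the cerebral NIRS oximeter or the application of the treatment guideline". It names no other data for the committee. It adds: "The charter for the DMSC will be written prior to inclusion of participants and prior to any analysis".

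Section 8.1.1 lists the expected reactions. Besides skin reactions and handling accidents it says: "Other expected adverse reactions encompass reactions to any interventions directed at correcting an out-of-range oximeter reading by improving respiratory status", and goes on to name cardiovascular status, oxygen transport and blood glucose. An expected serious adverse reaction (ESAR) is "any of the expected adverse reactions (listed above) that results in death, is life-threatening", or one that meets another seriousness criterion. A SUSAR is "an adverse reaction which is both serious and unexpected, i.e., not identified in the current risk analysis listed above".

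On deaths, section 8.1.4 says: "the mortality is high and will thus be analysed and reported as a secondary outcome measure and thus will not be reported to the authorities". Under section 8.1.5, sites send all serious adverse reactions, expected or not, to the sponsor within 24 hours. The sponsor then reports SUSARs quickly to the authorities and ESARs yearly.

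Section 8.4 says that the trial "can be suspended or prematurely terminated if the serious adverse device effects are considered disproportionately large compared to the possible benefits of the intervention". It gives decisions on continuation to the sponsor/principal investigator, the ethics committees and the regulators. The DMSC is not among them.

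**The concern.** Section 9 accepts that the intervention could do harm. The part most able to do so is the guideline, which prompts changes to respiratory and cardiovascular support. In extremely preterm infants such harm would seldom show as an isolated event that a clinician could confidently blame on the trial. It would show mainly as more deaths or more severe brain injury in one arm.

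The committee's stated remit filters on two features of the single case: that it is unexpected, and that it is certainly or probably related. Neither filter picks up an imbalance between arms. The first also removes most attributed guideline reactions before the committee sees them. At stake is whether an independent body sees the evidence of harm while the trial can still be changed.

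**Working it through.** The main check sets the sections side by side. No stated figure is in dispute.

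**Step 1: what the remit covers.** Section 8.3 names SUSARs rated certain or probable/likely, and nothing else.

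**Step 2: where a guideline-caused death falls.** The four domains in the expected list of 8.1.1 are respiratory status, cardiovascular status, oxygen transport and blood glucose. These are the four assessment headings of Appendix A, so the list covers essentially every guideline action. A reaction on the list that ends in death is an ESAR. A SUSAR must be off the list. A guideline-caused death is thus by default an ESAR, outside the remit. Yet 8.3 expects the committee to see SUSARs arising from the guideline, so the two sections do not fit together.

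**Step 3: the causality filter.** Table 4 counts only reactions rated certain or probable/likely. Table 3 allows probable/likely only when disease or other treatment is an unlikely cause. Section 8.1.4 says that serious events are to be expected in both groups whatever the allocation. Few deaths would meet that test; the rest are outcome data only.

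**Step 4: the stated routes during the trial.**

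| Event | Sponsor | Authorities | DMSC |
|---|---|---|---|
| SUSAR | within 24 hours | expedited | yes (8.3) |
| ESAR, including an attributed guideline death | within 24 hours | yearly and at end of trial; the yearly report may be replaced by the final one | none stated |
| Death not attributed | through the eCRF on schedule | not reported | none stated |
| Deaths compared by arm | none stated before the final analysis | none stated | none stated |

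Even at the end, section 10.2 tests mortality formally only if the primary outcome is significant.

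**Step 5: scale.** The inputs are mortality of about 20% (section 1.1) and 166 infants, 83 per group (Summary, Sample size).

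- Expected deaths: 166 × 0.20 = 33.2 in all, and 83 × 0.20 = 16.6 per group.
- Binomial 95% ranges: 23 to 44 in all, and 10 to 24 per group.

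**Step 6: what a by-arm comparison could show.** Let control mortality be 20% and assume a higher mortality p₂ in the experimental arm. With n = 83 per group, p̄ the mean of the two risks, a two-sided 5% test and twin clustering ignored:

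power = Φ{ [ (p₂ − 0.20) − 1.96·√(2p̄(1 − p̄)/n) ] / √( [0.20·0.80 + p₂(1 − p₂)]/n ) }

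For p₂ = 0.30, p̄ = 0.25. The numerator is 0.10 − 1.96 × 0.0672 = −0.0317 and the denominator is 0.0668, so power = Φ(−0.475) ≈ 0.32.

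| Assumed p₂ | Expected deaths of 83 | Power at full enrolment |
|---|---|---|
| 0.25 | 20.8 | 12% |
| 0.30 | 24.9 | 32% |
| 0.35 | 29.1 | 58% |
| 0.40 | 33.2 | 81% |

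Only a large excess would be detected reliably even with all infants. Interim tables are therefore for the committee's judgement, not for a formal test.

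**The case against.** The strongest reply is that the safety system is wider than section 8.3 alone, and much of this stands.

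- A reader might infer that the suspension rule in 8.4 leaves out harm from the guideline. It does not. Section 8.1.1 treats adverse reactions and adverse device effects as one term that covers both the oximeter and the guideline. A guideline-caused death is a serious adverse device effect and already a ground for suspension. Only an excess of deaths that nobody has attributed falls outside 8.4.
- A reader might infer that SUSARs are the only harm signal while the trial runs. Section 8.1.5 sends ESARs to the sponsor within 24 hours, and the sponsor can suspend the trial.
- A reader might infer that no guideline-caused death could ever reach the committee. The SUSAR definition also takes in events of imminent danger that call for prompt action to protect others, so exceptional guideline events could qualify. A gradual imbalance in deaths would not.
- The DMSC charter is a separate document and is not at hand. It may add mortality, ESARs or planned looks. It cannot be said that nobody independent will compare the arms.
- Early by-arm tables would be thin. Mortality and NEC are assessed at term date, about three months after birth. Ultrasound images are uploaded and read centrally, with chasing only a month after the last scan. This limits what the tables can hold; it is no reason to have none.

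What remains is that the protocol fixes the committee's purpose in words that leave out most guideline-related serious reactions and the by-arm deaths. A charter that went further would be at odds with 8.3 as written.

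**Conclusion.** The point holds in a limited form. It concerns a remit that is stated and set too narrowly, not detail left to another document. As written, most guideline-caused deaths and all-cause mortality by arm have no stated route to the independent committee, and 8.4 gives that committee no role.

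The documents do not support a claim that such deaths can never reach it, that they reach nobody, or that the trial could not be suspended for attributed guideline harm.

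In size, about 33 deaths are expected by term, and by default few would meet the remit. How few cannot be derived, because it depends on causality ratings and on the charter. The count assumes that the protocol's 20% applies to the enrolled infants; the power figures rest on assumed excess risks and ignore twin clustering.

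**What to change.** - **Section 8.3 and the charter.** State that the DMSC receives all serious adverse reactions, both ESARs and SUSARs, and closed by-arm tables of deaths to date at one or more pre-set enrolment points. Add NEC and centrally read severe ultrasound injury as far as they are available at each look. The number and timing of looks is for the sponsor and committee to choose; quarter points of enrolment are one option.
- **Section 8.4.** Name the DMSC's advisory role. Add a by-arm excess of deaths or serious harm, whether or not single cases were attributed to the intervention, as a ground for considering suspension.
- **Sections 8.1.1 and 8.3.** Reconcile the broad expected category with the statement that the committee monitors guideline-related SUSARs.

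The cost is an amendment of wording, a matching charter entry, and a small amount of extra unblinded reporting by someone outside the trial team. Term-date data will be incomplete at early looks, and central ultrasound reads would have to be run earlier if they are wanted. No look at the primary outcome is needed, so none of its alpha is spent.

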### **8.4 Suspension or premature termination of the clinical investigation**

The sponsor/principal investigator, the ECs, and the regulatory authorities can decide about trial continuation. The clinical investigation can be suspended or prematurely terminated if the serious adverse device effects are considered disproportionately large compared to the possible benefits of the intervention. If the trial is terminated or suspended the parents of all trial participants will be informed and appropriate follow-up will be assured. If sponsor/principal investigator terminates or suspends the trial the relevant ECs and regulatory authorities will be provided with a detailed written explanation of the termination or suspension.

The sponsor/principal investigator can upon completion of the analysis of the reason(s) for a suspension decide to lift the suspension, when the necessary corrective actions have been implemented. The investigators, ECs, and relevant regulatory authorities will be notified and provided with the relevant data supporting the decision.

Breaking of blinding will not be relevant in this trial, since group allocation is visible and the assessment of the adverse device effects in the control group are independent of rStO2 readings of the device.

## 9. Ethical Considerations

The research question; can monitoring of cerebral oxygen saturation levels in the first hours after birth and subsequent treatment according to pre-specified guidelines prevent brain injury and maybe death, can only be answered in the specified population, and there is a clear benefit to the premature patient population as a whole, should the research gain a positive outcome (research in the Research Ethics Committee group c) As there are no randomised clinical trials (RCT), thus no conclusive evidence, on the benefit and harms of NIRS monitoring in preterm infants, we find it ethically suitable that the control group receives 'treatment as usual'. All interventions proposed in the treatment guideline are commonly used in this patient group.

There is clinical equipoise, which means that there is genuine uncertainty over whether the cerebral oximeter and subsequent treatment will be beneficial or may even be harmful to the participants. Due to the clinical nature of the trial population, the premature infants, some stress reactions related to the manipulation during positing and re-positing of the cerebral NIRS oximeter sensors can occur. These are however not clinically evaluated to give substantially more risk or discomfort as compared to no intervention. To obtain evidence-based knowledge on the benefit and harms of cerebral monitoring using NIRS as part of clinical management of premature infants, a large-scale RCT is needed. The SafeBoosC phase II trial serves as a feasibility trial for such a large phase III trial.

The SafeBoosC trial will only start the randomisation of participants after approvals from the relevant ethics committees and competent authorities have been received and parental informed consent is obtained. All parents will receive written and oral information about the trial before they are asked for their written consent (see section 9.2 for further details). They will only enrol their new-born in the trial by their own free will and can withdraw their consent for participation at any time. If a parent wishes to withdraw the participation, the patient will be treated according to the respective hospital's standard procedures. The trial will be conducted in compliance with the guidelines of the Declaration of Helsinki in its latest form and the International Conference on Harmonization of Good Clinical Practice Guidelines (49) To avoid concern it has been decided that multiple births will be randomised together and undergo allocation to the same intervention.

### 9.1 Informed consent procedure

Parents of potential participants will be invited to enrol their preterm newborn, when possible, before delivery. Due to the nature of the intervention, if potential participants are found after their delivery, informed consent procedures must take place within 3 hrs. Surrogate informed consent is required

from both parents, unless one parent has power of attorney. The sponsor/sponsor delegate (qualified physician or nurse connected to the trial) will make contact and parents will be informed of the trial, given the Parent information sheet (Appendix F) for the trial, and told about the possibility of the assessor. The information consultation will be held in an undisturbed setting, preferably the department meeting facilities. The parents will be given 24 hours to ask questions and make a decision, before a written informed consent can be obtained from both parents. Parents will be given a copy of the informed consent. If the birth is sudden the time to make a decision will be shorter.

## **9.2 Risk of complication for participants**

The following procedure will be implemented to prevent and/or minimise risk of complication for participants.

### **Related to devices**

Correct reading of the monitor (mainly to prevent false reading which may lead to wrong treatment) is critical. The investigators will train local staff as appropriate and trained staff will closely supervise all participants during the intervention.

To minimise skin irritation related to the device, the oximeter will be moved to different location every 4 hours.

### **Related to application of the treatment guideline**

All investigators have been involved in the development of the guideline and have approved the final version. The treatment guideline does not contradict any current national clinical practices. The investigators will train local staff as appropriate and will be available for consultation as needed.

## **9.3 Benefit for participants**

The participants in both groups will receive careful attention from qualified physicians and hospital staff during the trial and a closer follow-up after hospital discharge compared to infants not enrolled into the trial.

